## Abstract

**Background:**

Metacarpal fractures are common, accounting for 40 % of all hand injuries. The use of plates for the fixation of these fractures allows early aggressive hand therapy post-operatively, reducing post-operative stiffness. Traditionally, bicortical fixation is the standard practice, where both dorsal and palmar cortices of the metacarpal are drilled through, with screws engaging both cortices. Recent biomechanical studies have shown that unicortical fixation, where only the near cortex is drilled and engaged by the screw, results in no difference in stiffness, load to failure or failure mechanism, when compared with bicortical fixation. This trial aims to compare fracture union, complication rate and functional outcomes between unicortical and bicortical fixation for adults with displaced metacarpal fractures.

**Methods/Design:**

All adults with displaced diaphyseal metacarpal fracture requiring plate fixation are potentially eligible to take part in this study. A total of 315 consenting patients will be randomly allocated to either unicortical or bicortical plate and screw fixation. The surgery will be performed in specialist hand trauma units across the UK. Data regarding fracture healing, hand function, quality of life, and complications will be collected at 2 weeks, 6 weeks and 6 months following surgery.

**Discussion:**

This pragmatic, prospective, multi-centre, randomized controlled trial is expected to deliver results in 2018.

**Trial registration:**

ISRCTN 18006607. Registered on 19 Nov 2015.

## Background

### Background and rationale

Metacarpal fractures are common, accounting for 40 % of all hand injuries; many can be treated non-operatively [1]. Surgery is reserved for cases in which an adequate reduction of both angular and rotational deformity cannot be maintained or where an adjacent ray is damaged. Metacarpal shaft fractures may be transverse, where the deformity is typically apex–dorsal. Fractures may also be spiral or oblique; these are more unstable, and reduction must restore rotational alignment as a first priority.

A variety of surgical strategies exist, including percutaneous Kirschner wiring, intramedullary fixation, and osteosynthesis with plate and screw construction [1]. The use of plates for the fixation of metacarpal fractures was first documented by Burton and Eudell in 1958 and became widespread in the 1970s and 1980s [2]. A plate secured along the dorsal midline of the metacarpal has been shown to be the best biomechanical method of fixation, with significantly more stability than Kirschner wiring or intramedullary fixation [3]. As a result, metacarpal plating allows earlier aggressive hand therapy post-operatively than alternative treatment methods, reducing post-operative stiffness. This is now the standard of care for unstable or displaced diaphyseal metacarpal fractures.

Traditionally, bicortical fixation is the standard practice, where both dorsal and palmar cortices of the metacarpal are drilled though and the screws engage both cortices. However, such practice is not without risk. In this method, the flexor tendons and neurovascular bundles are at risk from over-zealous drilling through the palmar cortex. Correct screw size selection is critical, as overly long screws can irritate and cause rupture of the flexor tendon [4]. More recently, the biomechanical superiority of bicortical fixation over unicortical fixation in metacarpal fractures has been questioned, as the predominant force acting on the metacarpal is apex–dorsal loading (bending in a palmar direction), owing to the action of the flexor tendons [5]. Unicortical fixation is a surgically less complex operation, can theoretically cause less damage to surrounding soft tissues and avoids the complications associated with incorrectly sized screws. This is currently the standard treatment for the fixation of maxillofacial fractures [6].

There is a paucity in the literature of studies comparing unicortical and bicortical internal fixation of fractures in the hand, with no clinical or *in-vivo* evidence. In cadaveric studies, Dona *et al*. [5] showed that there was no difference in the stiffness, load to failure or failure mechanism between unicortical and bicortical fixation of fractures in 18 freshly frozen human metacarpals. The mean load to failure was 596 N for the unicortical group and 541 N for the bicortical group, using a four-point bending protocol [5]. Afshar *et al*. [7] showed that bicortical fixation had a load to failure one-fifth greater than unicortical fixation in 20 cadaveric human metacarpals, with a mean load to failure of 370 N for unicortical fixation and 450 N for bicortical fixation, using cyclic loading. However, Afshar *et al*. [7] did not take into account the biomechanical advantage of an intact soft tissue envelope and conceded that they could not correlate their findings with the loads experienced by the patient during rehabilitation following surgical fixation [7]. Khalid *et al*. [8] showed that bicortical fixation resulted in higher pull-out strengths in 40 cadaveric human proximal phalanges, but recommended unicortical fixation for diaphyseal fractures, as the pull-out force far exceeds that generated by the flexor tendon in passive and active finger flexion [8]. In an animal fracture model, Ochman *et al*. [9] found that the stability of unicortical and bicortical locking and nonlocking plate fixation differed, with the maximum load to failure greater in locking fixation methods [9]. Locking plates can create unique problems in the hand, however. The stability of conventional bone plating systems is achieved when the head of the screw compresses the fixation plate to the bone as the screw is tightened, generating a precisely contoured fit. Locking plate and screw systems circumvent the need for precise plate adaptation and achieve stability through a device that ‘locks’ the screw to the plate while the screw shaft secures the bone [10]. Imprecisely contoured plates that are offset from the bone can interfere with the extensor mechanism, inhibiting tendon glide and causing bursa formation [9].

### Objectives

The primary objective is to compare union rates between unicortical and bicortical screw and plate fixation of diaphyseal metacarpal fractures. Patients will be assessed for fracture union 6 months after their fracture fixation using radiographs, assessed by an independent musculoskeletal radiologist and a senior consultant hand surgeon; a third consultant hand surgeon will be consulted for verification in cases where there is disagreement.

The secondary objectives are to compare the implant failure rate, complication rate and functional outcomes between the two groups. Functional outcome measures will include scores on the Disabilities of the Arm, Shoulder and Hand Outcome Measure, the Patient Evaluation Measure, the EuroQol five dimensions questionnaire, and a visual analogue scale for pain, function, movement and satisfaction, as well as a range-of-motion assessment of the affected wrist and finger.

## Methods/Design

### Design

This is a prospective, pragmatic, multi-centre, randomized controlled non-inferiority trial. This study was approved by the NHS Research and Ethics Committee (no 14/WM/1212, 12 December 2014) and the UK National Health Service (NHS) Coordinated System for Gaining NHS Permission (National Institutes for Health Research Clinical Research Network study ID 18642).

### Study setting

This study has commenced recruitment at University Hospitals Birmingham. Other specialist hand units including University Hospitals Coventry and Warwick and Queen Victoria Hospital, East Grinstead will aim to start recruitment in 2016.

### Eligibility criteria

Patients will be eligible for this study if they meet the following criteria:Male or female, aged 18 years or above and able to give informed consentDiagnosed with metacarpal diaphyseal, extra-articular fracturesThe treating surgeon believes that they would benefit from operative fixation of the fractureSuitable for regional axillary brachial plexus anaesthesia or general anaesthesiaSurgical fixation will be within 10 days of injury

Patients will be excluded from participation in this study if any of the following apply:Pregnant or intend to be pregnant in the next 6 monthsNon-osteoporotic pathological fracture or a previous fracture of the same metacarpalOther non-metacarpal injury to the same upper limb requiring surgeryMajor nerve injury (e.g., median, ulnar or radial), blood vessel or tendon injuryMulti-trauma patientRevision procedure i.e. previous fracture of  the same metacarpalKnown malignancyThere is evidence that the patient would be unable to adhere to trial procedures or complete questionnaires, e.g. because of cognitive impairment or intravenous drug abuse

### Recruitment, ethics and consent

Patients will be recruited from NHS clinics and accident and emergency departments of at least three teaching hospitals in England, which each have a specialist hand surgery unit. A member of the surgical team will introduce the trial to eligible patients; if patients would like more information, they will be given the trial patient information documentation and a member of the research team will be informed. Patients will usually have 24 hours to consider participation but will have a minimum of 60 min in exceptional circumstances (e.g. trauma theatre space available on the day of presentation). Written consent will be obtained by a member of the research team, which will include consent for the randomized data of the study to be published in scientific peer-reviewed journals. Baseline pre-operative assessments will be obtained following consent. Randomization will take place immediately before surgery.

### Trial interventions

All of the hospitals involved in this trial currently use both of the methods of fixation and all of the surgeons involved will be familiar with both techniques. Operative fixation of fractures will take place under an axillary brachial plexus regional anaesthetic block or a general anaesthetic block, according to the anaesthetist’s preference. Patients will be randomized immediately pre-operatively to the method of fixation using a trial management database program entitled ‘Clinical Research Tool’ (CREST), designed by University Hospitals Birmingham computer and information technology developers and the trial statistician. Patients will be blinded to their treatment throughout the trial duration.

In this trial, the details of the surgery will be left to the discretion of the surgeon to ensure that the results of the trial maintain external validity.

#### Fixation method

A 2.0 mm straight plate will be applied through an incision over the dorsal aspect of the hand. The details of the surgical approach will be left to the discretion of the surgeon. A minimum of two screws will be used on each side of the fracture to hold the fracture. For patients assigned to unicortical fixation, only the near cortex will be drilled and nonlocking screws only engaging the near cortex will be used to hold the reduction. For patients assigned to bicortical fixation, both the near and far cortices will be drilled and nonlocking screws will engage both cortices. The same type of plate and screws will be used for both fixation methods.

Patients will be blinded to their treatment regardless of the type of anaesthetic used. For patients undergoing a regional anaesthetic block, a visual drape will be used and audio-visual distraction will be available.

The method of closure will be left to the discretion of the surgeon. Both patient groups will have a bulky dressing following the operation; the dressing will not inhibit the movement of the fingers and will allow early controlled range-of-movement exercises.

### Participant timeline

Patients randomized into the two groups will receive standardized, written hand therapy advice detailing the exercises they need to perform for rehabilitation following their injuries. All participating patients in both groups will be advised to move their wrist and finger joints within comfort limits. Dressings will be removed after between 5 and 7 days in a dressings clinic. Two weeks after surgery, patients will be assessed by a hand therapist and begin formal, standardized, active range-of-movement exercises according to a pre-defined protocol. Hand therapists will be blinded to the method of fixation. Rehabilitation for both treatment groups will be the same. A record of any additional rehabilitation input (type of input and number of additional appointments), together with a record of any other investigations or interventions, will be requested as part of the 2 week, 6 week and 6 month clinical follow-ups and this will also form part of the trial dataset. Clinicians will assess the patients at 6 weeks and 6 months post-operatively and will not be blinded for the purpose of assessing radiographs for complications (Fig. 1).

**Fig. 1 Fig1:**
[figure not shown]
Participant timeline. CREST, Clinical Research Tool; DASH, Disabilities of Arm, Shoulder and Hand Outcome Measure; EQ-5D, EuroQol five dimensions questionnaire; PEM, Patient Evaluation Measure; ROM, range of motion; VAS, visual analogue scale.

Techniques common in long-term cohort studies will be used to ensure minimum loss to follow-up, such as collection of several contact addresses, telephone numbers and email addresses. Considerable efforts will be made by the trial team to keep in touch with patients throughout the trial by means of newsletters, telephone calls, mobile text messages and letters to ensure attendance.

### Outcome measures

Patient characteristics and baseline (pre-injury) functional status will be collected after consent to take part in the trial has been obtained. Structured information regarding other injuries that may affect outcome, e.g. previous wrist injury, will be collected. All patients will be included in the analysis. Assessments will be performed at 2 weeks, 6 weeks and 6 months following patients’ operation. Results will be collected by a blinded hand therapist.

#### Primary outcome measure

The primary outcome measure for this study will be assessment of fracture union at 6 months.

Three-view (anteroposterior, lateral, and oblique views) radiographs of the hand at admission, 6 weeks and 6 months will be independently evaluated by two observers (a consultant musculoskeletal radiologist and an orthopaedic hand surgeon). In situations where there is conflict, a third senior hand surgeon will be asked to assess the radiographs and cast a deciding vote. The initial fracture assessment will include fracture displacement and angulation measured on a standard Picture Archiving and Communication System workstation (Agfa Impax 6, Agfa Healthcare), and pre-existing osteoarthritis in the hand. Union assessment on post-operative radiographs will be based on visibility of fracture lucency on each view. Fracture union will be defined as ‘united’ if trabeculae are seen crossing sclerosis at the fracture, ‘partially united’ if part of a lucent fracture line is still seen, ‘probably united’ if there is no clear gap but the fracture cannot be defined as ‘united’ based on the criteria, and ‘not united’ if fracture lucency can be clearly seen. If the fracture is partially united, the ratio of width of bridging trabeculae to the entire fracture length will also be recorded as an objective measure of degree of fracture union. Assessment of surgical plate and screws will be recorded for lucency at the metal bone interface, migration or breakage.

#### Secondary outcome measures

##### Intra-operative parameters

Surgical time and fluoroscopy time will be recorded for each patient.

##### Disabilities of Arm, Shoulder and Hand Outcome Measure

This is a 30-item, self-reported questionnaire designed to provide a more general measure of physical function and symptoms in people with musculoskeletal disorders of the upper limb [11].

##### The Patient Evaluation Measure

This consists of 11 self-reported questions relating to subjective hand function, scored on a Likert scale of 1 to 7. Symptoms assessed are feeling, cold intolerance, pain, dexterity, wrist movement, subjective grip strength, daily activities, work appearance and a general assessment of wrist and hand function [12].

##### The EuroQol five dimensions questionnaire

This is a validated, generalized, quality-of-life questionnaire consisting of five domains related to daily activities, with a five-level answer possibility. The combination of answers leads to the quality-of-life score [13].

##### Visual analogue scale scores

These will be obtained for pain, movement, function and satisfaction based on a 0–100 scale.

##### Complications

All complications will be recorded.

##### Radiographic evaluation

Standard posterior-anterior, oblique and lateral radiographs will be taken at 6 weeks and 12 months after the procedure.

##### Stiffness

The Total Active Motion score, composite flexion, and wrist movement will be measured at each follow-up visit to assess range of motion.

### Sample size

Published data indicate a non-union rate of 8 % when plates and screws are used to fix metacarpal fractures [14]. Assuming this value in each group, a total of 252 patients (126 patients per group) would have an 80 % chance of demonstrating equivalence, with a margin of 10 %, of the failure rates of unicortical and bicortical fixation with 95 % confidence. From previous local audits of hand trauma studies, a drop-out rate of 20 % can be expected. Assuming a drop-out rate of 20 %, we would need 315 patients in total.

The level of 10 % is based on the limited data available currently on what differences could be expected after treating metacarpal fractures with bicortical fixation, compared with unicortical fixation.

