### Statistical analysis

Baseline data (e.g. age and sex) will be summarized to check comparability between treatment arms, and to highlight any characteristic differences between those individuals in the study. Standard statistical summaries (e.g. medians and quartiles or means and standard deviations, dependent on the distribution of the outcome) and graphical plots will be presented for the primary and secondary outcome measures.

Differences between treatment groups will be assessed on an intention-to-treat basis. Tests will be two-sided and considered to provide evidence for a significant difference if *P* < 0.05 (5 % significance level). Estimates of treatment effects will be presented with 95 % confidence intervals.

The temporal patterns of any complications will be presented graphically and, if appropriate, a time-to-event analysis (Kaplan–Meier survival analysis) will be used to assess the overall risk and risks within individual classes of complications (e.g. implant failure).

Missing data are not expected to be a problem for this study. If the degree of data loss is relatively low, the primary analysis will be based on complete cases only, with analysis of imputed datasets used to assess the sensitivity of the analysis to the missing data. If the level of missing data is higher than expected, missing data will be imputed using the multiple imputation facilities available in R (http://www.r-project.org/).

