## Discussion

The SUBMIT trial is, to our knowledge, the first clinical trial to assess the efficacy of unicortical screw and plate fixation in patients with metacarpal fractures. Unicortical plate and screw fixation of metacarpal fractures is a less technically demanding and quicker procedure with, theoretically, less soft tissue disruption and potentially fewer complications.

Published studies have not proven a superiority of one fixation method over the other in cadaveric models. This study has been designed as a non-inferiority trial. We believe that should this study demonstrate equivalence between unicortical and bicortical fixation, unicortical fixation may become the standard method of fixing metacarpal fractures requiring surgery in the future.

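### The stated 80 % power belongs to an equivalence test judged on a 90 % interval, not to the non-inferiority design that the protocol declares

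*Protocol article*

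**What the plan says.** The Sample size section starts from this rate: "Published data indicate a non-union rate of 8 % when plates and screws are used to fix metacarpal fractures". With that rate in both groups, it gives 252 patients, 126 per group, an 80 % "chance of demonstrating equivalence, with a margin of" 10 %, "of the failure rates of unicortical and bicortical fixation with 95 % confidence". An allowance of 20 % for drop-out brings the total to 315. The section does not say whether the confidence level is one-sided or two-sided.

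The Design section names a different hypothesis: "This is a prospective, pragmatic, multi-centre, randomized controlled non-inferiority trial". The Discussion agrees ("This study has been designed as a non-inferiority trial"), but its next sentence makes a change in standard practice depend on showing equivalence.

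The Statistical analysis section sets two-sided tests at the 5 % level for a significant difference. On intervals it says "Estimates of treatment effects will be presented with" 95 % limits. The article mentions neither a 90 % interval nor a one-sided 5 % level, and it does not say which interval is compared with the margin.

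**The concern.** Equivalence and non-inferiority are different hypotheses. Equivalence needs both confidence limits inside ±10 points; non-inferiority needs only the upper limit for the excess of non-union with unicortical fixation to be below 10 points. A power figure belongs to one hypothesis at one error rate. Here the hypothesis in the sample size differs from the declared one, and the only interval named in the analysis differs from the one that yields the stated power.

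Two things are at stake. A reader cannot tell what chance of success the trial has, or what error rate its claim carries. And if the choice stays open until the data are seen, a result that lies inside the margin on a 90 % interval but outside it on a 95 % interval could be reported either way.

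**Working it through.** **Inputs** (Sample size section; the 1:1 ratio is in Patient allocation): non-union p = 0.08 in each arm, true difference 0, margin m = 0.10, n = 126 evaluable per group, power 80 %.

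**Common quantities**
- Variance term: 2p(1 − p) = 2 × 0.08 × 0.92 = 0.1472; divided by m² = 0.01 this is 14.72.
- Standard error at n = 126: √(0.1472/126) = 0.0342.
- Margin over standard error: 0.10/0.03418 = 2.926.

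**Reproducing the plan's figure.** For equivalence by two one-sided tests at level α each, n = 14.72 × (z₁₋α + z₁₋β/₂)² and power = 2Φ(2.926 − z₁₋α) − 1. With α = 0.05 per side:
- n = 14.72 × (1.645 + 1.282)² = 126.06 (unrounded z values).
- Power at 126 = 2Φ(1.281) − 1 = 80.0 %.
- Drop-out: 252/(1 − 0.20) = 315.

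So 126, 80 % and 315 all follow, apart from rounding 126.06 down.

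**The other readings.** For non-inferiority, n = 14.72 × (z₁₋α + z₁₋β)² and power = Φ(2.926 − z₁₋α).

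| Hypothesis | Error per side (interval) | Power at 126 per group | n per group for 80 % |
|---|---|---|---|
| Equivalence | 5 % (90 %) | 80.0 % | 126.06 |
| Equivalence | 2.5 % (95 %) | 2Φ(0.966) − 1 = 66.6 % | 154.7, so 155 |
| Non-inferiority | 2.5 % (two-sided 95 %) | Φ(0.966) = 83.3 % | 115.5, so 116 |
| Non-inferiority | 5 % (two-sided 90 %) | Φ(1.281) = 90.0 % | 91.01, so 92 |

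Sizing for superiority, 8 % against 18 %, gives 139 to 196 per group depending on sidedness and continuity correction. Non-inferiority at one-sided 5 % also leads to 126.06, but for 90 % power, not the stated 80 %.

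**Sensitivity to the interval method.** Summing exact binomial probabilities at n = 126 gives:
- Wald limits: equivalence 79.6 % (90 % interval) and 66.2 % (95 %); non-inferiority 83.1 % (95 %) and 89.8 % (90 %).
- Newcombe limits: equivalence 77.2 % (90 %) and 59.1 % (95 %); non-inferiority 79.6 % (95 %) and 88.6 % (90 %).

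**The case against.** The strongest reply is that nothing has been miscalculated. Two one-sided tests at 5 % each form a 5 % level equivalence test, and 95 % confidence is a natural way to describe that. This stands. A reader might infer that the sample size is an arithmetic error or that the confidence statement is false; the documents support neither.

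A second tempting reading is that the trial is underpowered at 67 %. That figure needs the 95 % interval to decide an equivalence claim. The Statistical analysis section says only that estimates are presented with 95 % intervals, which is compatible with a decision made at 5 % per side. The 67 % is therefore conditional, and under the declared non-inferiority design the planned number is enough. Nor can one say that the equivalence test will not be run, since the Discussion still hopes to show equivalence.

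Third, the interval for the decision may be fixed in a statistical analysis plan that is not shown, and the article names no interval method, so the Newcombe figures are a sensitivity check and not a test of anything the plan states. Both are fair. With Newcombe limits, non-inferiority at one-sided 2.5 % also happens to come close to 80 %; the statement that only equivalence reproduces the stated pairing applies to the normal approximation.

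What the reply does not remove is the conflict within the article itself. It prints one hypothesis in the sample size and another in the design, and its only stated test addresses neither. That is not an omission that a later document could excuse.

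**Conclusion.** The inconsistency is real and sits in hypothesis, error rate and interval, not in the calculation. The stated 80 % describes equivalence at 5 % per side. For the declared non-inferiority design, the power at 126 evaluable per group is about 83 % at one-sided 2.5 % (about 80 % with Newcombe limits) or 90 % at one-sided 5 %. If equivalence were judged on a 95 % interval it would be about 67 % (59 % with Newcombe limits).

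These figures rest on the plan's own assumptions: 8 % non-union in both arms, no true difference, and 126 evaluable patients per group after drop-out. Only equivalence claimed from a 95 % interval leaves the trial clearly short of 80 %, and the article does not specify that combination. The point should be settled before analysis because the confirmatory claim depends on it.

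**What to change.** Keep 315 patients. State one hypothesis, its one-sided error rate and the matching interval, and use them in the Design, Sample size, Statistical analysis and Discussion sections alike.

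- **If non-inferiority, as declared:** unicortical fixation is non-inferior if the upper limit of the two-sided 95 % interval for the difference in non-union (unicortical minus bicortical) is below 10 percentage points. Give the power at 126 evaluable per group as about 83 % (about 80 % with Newcombe limits), and replace the term equivalence in the Sample size and Discussion sections.
- **If equivalence is intended:** change the Design and Discussion sections, and state either a 90 % interval with 5 % error per side (80 % power) or a 95 % interval (about 67 %).

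In either case, replace the two-sided significant-difference rule for the primary outcome with this comparison of the interval with the margin. Rewording the sample-size paragraph alone would leave the analysis section without a test of the trial's hypothesis.

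The cost is a few reworded paragraphs and no extra patients. Only a choice of equivalence on a 95 % interval with 80 % power kept would need more: 155 per group, 310 evaluable, 310/0.80 = 387.5, so 388 in total, which is 73 above the present target.
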